## Abstract

**Background::**

Diabetic foot (DF) is among the most serious complications of type 2 diabetes. DF infection (DFI) is a key factor in the deterioration and development of DF, so controlling infection plays an important role in the treatment of the disease. Traditional Chinese medicine foot bath has been widely used in China as a complementary and alternative therapy to improve circulation and infection control of DF. However, the existing evidence shows that its efficacy and safety are still insufficient. We report a study protocol about a multicenter, double-blind, randomized, placebo controlled trial which aims to make well-designed clinical trials to evaluate the efficacy and safety of herbal medicine foot bath decoction (FBD) and explore the mechanism of external washing of Chinese herbs in DFI.

**Methods::**

This study is a multicenter, double-blind, randomized, placebo controlled clinical trial in which 60 eligible participants were randomly divided into an experimental group and control group at a 1:2 ratio. Both groups received the same basic treatment for DF disease, the experimental group used FBD and ordinary dressing changes, while half of the patients in the control group received placebo and ordinary dressings, and the other half received placebo and silver ion dressings. Patients in both groups will be evaluated weekly for efficacy during the intervention. The primary efficacy indicators include the types of wound pathogens, interleukin 6 and tumor necrosis factor α. Secondary efficacy indicators included blood glucose, blood lipids, wound area, lower extremity blood vessel diameter, blood flow speed, walking speed, walking distance, and traditional Chinese medicine syndrome scores. We will also conduct a safety evaluation of the drug at the end of the trial.

**Discussion::**

This multicenter, double-blind, randomized, placebo clinical trial not only provides data on the efficacy and safety of FBD, but also provides a novel treatment strategy for clinicians and DF patients.

## Introduction

1

Diabetic foot (DF) is a globally prevalent chronic complication that causes an increased risk of lower limb amputation and death in diabetic individuals.^[1]^ It is reported that about 1 in 4 people with diabetes will suffer from DF during their lifetime, and the point prevalence rate is almost 2%.^[2,3]^ Along with this, engaging in medical care related to DF has placed a huge economic burden to patients and the society.^[4]^ DF usually has a poor prognosis. According to a retrospective study in China, the proportion of amputations caused by DF is 19.03% to 27.3%.^[5,6]^ DF infection (DFI) is the foremost cause of the occurrence and progression of DF ulcers, and the susceptibility factors are closely related to autoimmune deficiency, neuropathy, and arterial disease.^[7]^

The pathologic process of DF is very complicated, involved in damaged skin, muscle, tendon, bone, nerve, and blood vessel. The DFI refers to the invasion of microorganisms and its reproduction in host tissues, which usually begins with the dehiscence of the shielding skin envelope and plays an indispensable role in the above process.^[8]^ The treatment of DF advocates a multidisciplinary combination of endocrinology, dermatology, vascular surgery, and orthopedics,^[9–11]^ which involves controlling blood glucose, reducing blood pressure, ulcer debridement, reducing stress, controlling infection, and rebuilding blood circulation.^[12,13]^Although the use of antibiotics is an indispensable means of controlling DFI, the abuse of antibiotics and the presence of drug-resistant bacteria make this treatment process more difficult. In addition, given that some antibiotics may cause liver damage, nephrotoxicity, and a range of adverse reactions of the digestive system in the digestive tract.^[14]^ Therefore, seeking personalized therapy and new complementary drugs to control infection have not stopped.

In recent years, most patients with DF in China are adopting a treatment method that combines traditional Chinese medicine (TCM) and western medicine. Foot bath, with a history of thousands of years, is widely used in traditional medicine to treat surgical diseases, especially infectious wounds. Foot bath decoction (FBD) is a TCM compound consisting of Raw Rhubarb (Shengdahuang), Coptidis Rhizoma (Huanglian), Fructus Forsythia (Lianqiao), aluminum potassium sulfate (Kufan), Pseudobulbus Cremastrae Seu Pleiones (Shancigu). Modern pharmacologic researches have shown that Rhein, the main active ingredient of Raw Rhubarb, has obvious effects in promoting metabolism, anti-inflammatory, antibacterial, analgesic, and improving circulation.^[15,16]^ Coptidis Rhizoma has been used to treat various inflammatory disorders and related diseases for a thousand years, and various modern studies have demonstrated that Coptidis Rhizoma has wide pharmacologic activities, including antibacterial, antifungal, antiatherosclerosis, antimyocardial ischemia/reperfusion injury, antidiabetic, anti-inflammation, antioxidation.^[17,18]^ Considering that Fructus Forsythia has a strong anti-inflammatory effect and acts as a broad spectrum antimicrobial agent, it is widely used in chronic and acute inflammation. Some research confirm that Fructus Forsythia's anti-inflammatory activity ranks among top 5 of 81 tested Chinese medicines.^[19,20]^ Numerous animal experiments present that aluminum potassium sulfate can inhibit the growth of anaerobic and facultative anaerobic bacteria.^[21]^ A variety of active compounds in Pseudobulbus Cremastrae Seu Pleiones have antibacterial effects, especially against *Pseudomonas aeruginosa*, *Staphylococcus epidermidis*, and *Staphylococcus aureus*.^[22]^ Therefore, the FBD has the functions of clearing heat, detoxifying, and eliminating evil from the theory of TCM. It is reasonable to assume that FBD is effective in the treatment of DFIs. However, there is no direct evidence to support its efficacy and safety.

Recently meta-analysis has shown that TCM foot bath can significantly improve the sensory nerve conduction velocity, motor nerve conduction velocity, and neuropathy syndrome scores in patients with diabetic peripheral neuropathy, and has certain advantages in alleviating its clinical symptoms.^[23]^ Foot bath can inhibit bacteria through the environmental changes on the surface of foot ulcers. Several studies have shown that the anti-inflammatory effect of herbal medicine foot bath may be achieved by lowering blood glucose and reducing the number of hypersensitive C-reactive protein and white blood cells.^[24]^ Based on the above conclusions, we hypothesized that FBD can both regulate and inhibit local bacteria to promote healing of DF wounds.

## Methods and design

2

### Design

2.1

This study is a multicenter, double-blind, randomized, placebo controlled clinical trial, and the protocol was registered in Chinese Clinical Trial Registry on July 16, 2019, ChiCTR1900024557. Sixty eligible participants signed the informed consent and were randomly assigned to the experimental or control group at a ratio of 1:2. Both groups received the same basic treatment for DF disease, the experimental group was additionally washed with FBD and ordinary dressing changes, while half of the patients in the control group received placebo and ordinary dressings, and the other half received placebo and silver ion dressings. The purpose of this trial is to explain the efficacy and safety of herbal medicine FBD for DFI compared with western medicine (WM) alone. This study will adhere to the standard protocol items: Recommendations for Interventional Trials (SPIRIT) 2013 statement, and flow chart of the study will be used to show the screening process (Fig. 1).

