### Test drugs

2.10

Test drugs including FBD and placebo were prepared by the Department of Pharmacy of the Affiliated Hospital of Chengdu University of Traditional Chinese Medicine. The composition of the FBD is as follows: Raw Rhubarb (Sheng dahuang) 20 g, Coptidis Rhizoma (Huang lian) 15 g, Fructus Forsythia (Lian qiao) 15 g, Aluminum potassium sulfate (Ku fan) 10 g, Pseudobulbus Cremastrae Seu Pleiones (Shan cigu) 10 g. All herbs are mixed, soaked, cooked, and made into a single-dose pouch of uniform specifications by the pharmacy department, each bag is about 150 mL. Placebos are made from starch without active ingredients and added a variety of food colors. The placebo was consistent with the FBD in color, odor, and dosage. Furthermore, the ordinary dressings and silver ion dressings should also have no difference in appearance and smell.

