### Treatment plan

3.1

Both groups received based on dietary treatments recommended by the Diabetes UK evidence-based nutrition guidelines for the prevention and management of diabetes,^[29]^ and controlled blood glucose, lowered blood lipids, adjusted blood pressure, and suppressed infections according to individual conditions during the trial period. At the same time, DF ulcers can be treated by surgical debridement to remove necrotic tissue, improve lower limb circulation and a routine dressing every 2 to 3 days according to the Diabetic Foot Ulcer Treatment Guidelines.^[30]^

Experimental group: The participants in experimental group took a foot bath 1 to 2 times a day. Each bag of FBD was dissolved in 300 mL of warm water for 30 minutes, then cover the wound with a ordinary dressing.

Control group: The patients in the control group will be given a placebo decoction for foot bath twice daily for 30 minutes. The immersion method is the same as the experimental group. In contrast, half of the patients covered the wound with an ordinary dressing and half with a silver ion dressing.

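### The stated purpose compares FBD with western medicine alone, but every control patient also has a placebo foot bath and half have silver ion dressings, so the objective and conclusions should name the contrast actually randomised

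*Protocol article*

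**What the plan says.** All references are to the protocol article.

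- **Purpose (2.1 Design).** The trial is to "explain the efficacy and safety of herbal medicine FBD for DFI compared with western medicine (WM) alone".
- **Design label (2.1 Design).** "This study is a multicenter, double-blind, randomized, placebo controlled clinical trial, and the protocol was registered".
- **Background care (2.1 Design).** "Both groups received the same basic treatment for DF disease".
- **Control bath (3.1 Treatment plan).** "The patients in the control group will be given a placebo decoction for foot bath twice daily for 30 minutes".
- **Control dressing (3.1 Treatment plan).** "half of the patients covered the wound with an ordinary dressing and half with a silver ion dressing". The experimental group has the ordinary dressing only.
- **Experimental bath (3.1 Treatment plan).** "The participants in experimental group took a foot bath 1 to 2 times a day".
- **Placebo content (2.10 Test drugs).** "Placebos are made from starch without active ingredients and added a variety of food colors".
- **Action of a foot bath (Introduction).** "Foot bath can inhibit bacteria through the environmental changes on the surface of foot ulcers".
- **Numbers (2.4 Sample size).** 20 experimental and 40 control patients.
- **Safety analysis (3.5 Statistical analysis).** Adverse-event incidence is compared between the two groups by a chi-squared or Fisher exact test.

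**The concern.** The purpose sentence names a comparator that nobody in the trial receives. A reader who takes section 2.1 at its word would expect the result to say what happens when FBD baths are added to usual care without a bath. The randomised groups do not differ in that way, because the controls soak the foot too.

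This would not matter if soaking were known to do nothing to an ulcer. The protocol does not establish that. One sentence in the Introduction gives some ground to think otherwise, and wound pathogens are among the primary outcomes in section 3.2.

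Two kinds of conclusion are at stake:

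- **Efficacy.** If soaking helps, the observed difference understates FBD against care without a bath. If soaking harms, FBD could beat the placebo bath without being better than care without a bath.
- **Safety.** Harms of soaking can occur in both groups, so a between-group test has little ability to show them. Finding no difference would not show that FBD is as safe as western medicine alone.

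**Working it through.** **Step 1. Who receives what.** Sixty patients at 1:2 gives 60 × 1/3 = 20 experimental and 60 × 2/3 = 40 control, which matches section 2.4. Half of 40 is 20.

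| Patients | Basic treatment | Bath | Dressing |
|---|---|---|---|
| 20 experimental | yes | FBD | ordinary |
| 20 control | yes | placebo | ordinary |
| 20 control | yes | placebo | silver ion |
| 0 | yes | none | any |

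The last row is the comparator named in the purpose sentence, and it is empty.

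**Step 2. What the contrast estimates.** Take a simple additive sketch in which positive values mean benefit. This is an assumption made for clarity; the documents give no such model. Let

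- B = result under basic treatment with an ordinary dressing and no bath
- H = effect of the FBD ingredients
- S_e, S_c = effect of soaking itself at the bath frequency of the experimental and control group
- D = effect of a silver ion dressing relative to an ordinary one

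Then:

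- Experimental mean = B + H + S_e
- Control mean = B + S_c + D/2, since half the controls have silver
- Randomised difference = H + (S_e − S_c) − D/2
- Stated question, FBD bath against B = H + S_e
- Stated question minus randomised difference = S_c + D/2

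If silver ion dressings are instead counted as part of western medicine, the named comparator becomes B + D/2 and the gap reduces to S_c. On either reading the gap contains S_c, the effect of the control group's own soaking. No arm without a bath exists from which to estimate it.

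**Step 3. Can the gap be sized?** No. The documents give no value for S_e, S_c or D. The IL-6 means in section 2.4 (6.14 and 6.21) are labelled experimental and control group, and the control group here has a placebo bath. Nothing says that their difference, 0.07, was a difference against care without a bath, so there is no basis for subtracting a share of it for soaking.

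**Step 4. Is soaking equal in the two groups?** Section 3.1 gives the experimental group 1 to 2 baths a day, which is 7 to 14 a week, and the control group 2 a day, which is 14 a week. The number of baths matches only at the upper end of the experimental range. So S_e = S_c is not assured, and effects of soaking are largely shared rather than removed exactly.

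**Step 5. Other statements of aim.** The Abstract and the Discussion speak of the efficacy and safety, or risks and benefits, of FBD without naming western medicine alone as the comparator. The mismatch sits in the one purpose sentence of section 2.1.

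**The case against.** The strongest reply is that this is a slip in one phrase. The same section calls the trial placebo controlled, gives both groups the same basic care and says that controls receive placebo. A colleague could fairly read western medicine alone as basic treatment without active FBD. A placebo bath on common background care is the usual way to blind an add-on comparison, and it suits a hypothesis about the herbal ingredients. All of this stands as a defence of the design. It does not make the sentence correct, and the sentence fixes what the conclusion will claim.

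Four stronger readings are tempting and are not supported:

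- **That the protocol itself regards the placebo bath as antibacterial.** It does not say so. The Introduction's sentence is general, stands in a paragraph on traditional and herbal baths, and leads to a hypothesis about FBD. Section 2.10 describes the placebo as free of active ingredients. That description concerns content, though, and not the act of soaking, so neutrality is unproven rather than denied.
- **That the trial can answer nothing on efficacy or safety.** It can answer the question of FBD bath against placebo bath, with the dressings as assigned.
- **That a percentage of bias or lost power can be attached.** Any such figure would need an invented share for the bath, and the adequacy of the sample size is a separate matter.
- **That harms of soaking cancel completely.** The bath frequencies differ, so this is not established.

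It may also be said that arm-level event rates are reporting detail for an analysis plan that is not shown. Their absence from the article is therefore not treated as a fault. They are suggested because they support the narrower safety statement.

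**Conclusion.** The point holds as a mismatch between the stated objective and the comparator delivered. Of 40 controls, 40 have a placebo bath, 20 have a silver ion dressing and none has western medicine alone without a bath. The trial supports a conclusion about FBD bath plus ordinary dressing against placebo bath plus ordinary or silver ion dressing, on common basic treatment. It does not isolate the herbal ingredients, because of the silver dressings and the unequal bath frequencies. It does not compare FBD with care that includes no bath.

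The factual part rests only on sections 2.1, 2.4 and 3.1. The consequence for interpretation rests on soaking not being known to be neutral. If soaking had no effect, the randomised contrast would also answer the stated question, apart from the silver ion dressings where these are not counted as western medicine. The size of the discrepancy in effect is unknown. The placebo design itself is not at fault, and the correction is small, but it governs what may be claimed.

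**What to change.** - **Section 2.1.** Replace the comparator in the purpose sentence, so that it reads: *FBD foot bath plus ordinary dressing compared with placebo foot bath plus ordinary or silver ion dressing, both added to the same basic treatment*.
- **Conclusions.** Limit efficacy and safety statements to that contrast, and say that no claim will be made against western medicine without a bath.
- **Section 3.5.** Show adverse-event rates in each arm alongside the between-group test, so that events common to both groups remain visible.
- **Section 3.1.** Reconcile the bath frequencies given for the two groups. Which frequency applies is for the investigators to settle.

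The cost is a few sentences and one descriptive table, with no extra patients or procedures. The downside is a narrower claim.

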**Figure 1 F1:**
[figure not shown]
Flow chart of the study.

### Ethics and dissemination

2.2

The study is in compliance with the Declaration of Helsinki (Edinburgh 2000 version). The program was approved by the Ethics Committee of Sichuan Traditional Chinese Medicine Regional Ethics Review Committee Chengdu University of TCM Teaching Hospital Ethics Committee (Code 2019KL-020). If there are any additions or amendments to the protocol during the research, the consent of the ethics committee must be obtained again.

### Recruitment

2.3

This study is a multicenter clinical trial. The recruitment area involves 3 hospitals, namely Hospital of Chengdu University of Traditional Chinese Medicine, Shuangliu District Traditional Chinese Medicine Hospital and Mianyang Traditional Chinese Medicine Hospital. It should be noted that the main sponsor is Hospital of Chengdu University of Traditional Chinese Medicine. Recruit participants by posting posters at various hospitals. Before signing an informed written consent, participants will be familiar with all the details of the clinical study and the potential risks and benefits.

### Sample size

2.4

This study is a superiority clinical trial with interleukin 6 (IL-6) as the main efficacy indicator, so we chose the mean superiority test of 2 independent samples to estimate the sample size. According to the previous relevant references,^[25]^ the optimal response rate was set to 0.04. The mean values of the experimental group and the control group were 6.14 and 6.21, and the combined standard deviation of the 2 groups was 0.14. At the same time, set *a* to 0.025 and *b* to 0.2. Enter the above values into the Power Analysis and Sample Size version 11.0 (PASS 11.0) software to calculate the sample size for the experimental group as 20 and the control group as 40. Finally, the total number of study samples is determined to be 60 cases.

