### Statistical analysis

3.5

The data of the study will be analyzed by statistical analysis software packages SPSS 23.0 and will be performed by experts from the Statistics Teaching and Research Office of Chengdu University of Traditional Chinese Medicine. The measurement results was calculated by *t* test, and the results were expressed as “mean ± standard deviation.” Chi-squared test was used to analyze the count data. The paired design *t* test was used for comparison the differences between before and after treatment with the same group, and the independent sample *t* test was used for comparison the differences between groups. The comparison of incidence of adverse events between the 2 groups using Chi-squared test or Fisher exact probability method. If *P* < .05, it was considered as a statistically significant difference.

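### The inputs in section 2.4 do not give 20 + 40: for the planned t test that size has about 43% power for the 0.07 difference in IL-6, not the implied 80%

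*Protocol article*

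**What the plan says.** Section 2.4 (Sample size) of the protocol article sets the aim: "This study is a superiority clinical trial with interleukin 6 (IL-6) as the main efficacy indicator". It says that a superiority test for two independent means was used, and it lists the inputs. The first of them are: "the optimal response rate was set to 0.04. The mean values of the experimental group and the control group were 6.14 and 6.21". For the spread, "the combined standard deviation of the 2 groups was 0.14". For the error rates, the authors "set *a* to 0.025 and *b* to 0.2". The values were entered in PASS 11.0 to "calculate the sample size for the experimental group as 20 and the control group as 40", 60 in all. Section 2.1 (Design) gives the 1:2 allocation.

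Section 3.5 (Statistical analysis) names the between-group test for measured outcomes: the independent-sample t "test was used for comparison the differences between groups". The significance threshold there is 0.05. No margin appears in section 3.5, and neither section says whether its level is one- or two-sided.

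**The concern.** Every input needed to check the sample size is printed, and the result does not follow from them. The assumed difference is half a standard deviation (0.07 / 0.14 = 0.5), and a 1:2 trial of 60 patients is small for 80% power at that effect size. The 0.04 adds a second difficulty. It is labelled as a response rate, which is not an input to a comparison of two means, so its role in the calculation is unclear.

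At stake is the only sample-size justification in the document. If power for the planning difference is below one half, the trial is more likely to miss that difference than to detect it. A reader who trusts the implied 80% would then give a non-significant IL-6 result more weight than it can bear.

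**Working it through.** **Inputs.** From section 2.4: means 6.14 and 6.21, so a difference of 0.07; SD 0.14; alpha 0.025; beta 0.2; the value 0.04; sizes 20 and 40. From section 2.1: allocation 1:2. Assumptions: alpha 0.025 is one-sided, which matches a two-sided 0.05 test in section 3.5 (the other reading is shown below); lower IL-6 is better, because the experimental mean is the smaller one; no allowance for dropout.

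**Size formula (normal approximation, 1:2).** Experimental n = 1.5 × (1.960 + 0.842)² × 0.14² / d² ≈ 0.2308 / d², with control = 2n. The noncentral t gives the exact sizes.

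**Reproducing the plan's 20 + 40.** Three superiority readings of the stated inputs fail, and one other distance succeeds:

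| Distance d | Reading | Normal approximation, n | Smallest 1:2 size for 80% (t) | Power of 20 + 40 (t) |
|---|---|---|---|---|
| 0.07 | plain superiority | 0.2308 / 0.0049 = 47.1 | 48 + 96 = 144 | 43.5% |
| 0.07 − 0.04 = 0.03 | superiority by a 0.04 margin | 0.2308 / 0.0009 = 256.4 | 258 + 516 = 774 | 11.7% |
| 0.04 | 0.04 taken as the effect | 0.2308 / 0.0016 = 144.3 | 145 + 290 = 435 | 17.5% |
| 0.07 + 0.04 = 0.11 | 0.04 added to the difference | 0.2308 / 0.0121 = 19.1 | 20 + 40 = 60 | 80.5% |

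At distance 0.11, 19 + 38 gives 78.4%, so 20 + 40 is the smallest 1:2 size that reaches 80%.

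**Power of the planned test by hand.** The standard error of the difference is 0.14 × √(1/20 + 1/40) = 0.14 × 0.2739 = 0.0383. For d = 0.07 the standardised difference is 0.07 / 0.0383 = 1.826. The normal approximation gives Φ(1.826 − 1.960) = Φ(−0.134) = 44.7%; the noncentral t with 58 degrees of freedom gives 43.5%.

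**Sensitivity to sidedness, d = 0.07 (t).**
- One-sided 0.025, or two-sided 0.05: 43%.
- Two-sided 0.025: 32%, and 80% power would need 58 + 116 = 174.
- One-sided 0.05, which departs from the stated alpha: 56%, and 80% power would need 38 + 76 = 114.

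**Detectable difference.** With 20 + 40 at one-sided 0.025, 80% power is reached at a difference of 0.109. That is 0.109 / 0.14 = 0.78 SD, and 0.109 / 0.07 = 1.56 times the planning difference.

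**The case against.** The strongest objection concerns the cause. Section 2.4 never calls 0.04 a margin and never mentions non-inferiority, and neither the software entries nor the cited source can be seen. This stands: addition of 0.04 is an inference from an exact numerical match. The match does not show whether a non-inferiority procedure was chosen or a sign was mis-entered in a superiority procedure. The match is also not unique once the stated inputs are relaxed. A difference of 0.07 with SD 0.14/√2 and one-sided alpha 0.05 also returns 20 + 40. That route contradicts the stated SD and alpha and leaves 0.04 unused, so it does not rescue the plan. The 43% depends on neither explanation.

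A second objection is that the Discussion already lists the small sample as a limitation and asks for larger studies. That tempers how a null result might be read, but it is a general remark and does not correct the figures in section 2.4.

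Two stronger readings are tempting. A reader might infer that the trial's power is really 12%. That figure applies only if 0.04 was meant as a superiority margin, and the t test in section 3.5 uses none. A reader might also infer that the trial will end in an empty non-inferiority claim against placebo. The document plans no such claim, and half the control group also receives silver ion dressings, so the comparator is not simply placebo.

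**Conclusion.** The point holds. As a superiority calculation, the inputs in section 2.4 do not yield 20 + 40. For the planned t test and the 0.07 planning difference, power is about 43% if alpha 0.025 is one-sided and about 32% if it is two-sided, against the 80% implied by beta 0.2. At one-sided 0.025, 80% power would need 144 patients.

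This rests on the printed means and SD, 1:2 allocation, a two-group t test and no dropout. Addition of 0.04 to the difference is the likely origin of the stated size but is not demonstrated. The 12% figure is conditional on a margin that the planned analysis does not use.

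**What to change.** Amend section 2.4 as follows:

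- Define the 0.04 and its role, or delete it.
- State the hypothesis as superiority with zero margin, to match section 3.5.
- State whether alpha 0.025 is one- or two-sided.
- With alpha stated as one-sided 0.025, restate the power of 20 + 40 as about 43% for a difference of 0.07, with 80% power only for a difference of about 0.109 (0.78 SD).

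Report the IL-6 difference with its 95% confidence interval, and do not rest a null conclusion on 80% power.

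The cost is a less favourable power statement and an amendment, for which section 2.2 requires renewed ethics committee consent. No extra patients are needed. If the sponsor prefers to keep 80% power for 0.07, the price at one-sided 0.025 is 144 − 60 = 84 more patients. Calling the trial exploratory is a further choice for the sponsor; the correction does not depend on it.

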### Termination and withdrawal criteria

2.9

All participants were informed that they had the right to drop out of the study before starting the experiment. The test will also be withdrawn or terminated if the following criteria occur.

1.Side effects and adverse reactions occur, which are difficult for patients to tolerate.2.Serious adverse events occurred.3.Complicated with other diseases during the test.4.Patients with poor compliance and failed to perform research protocol as required.

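### Section 2.4 randomises exactly the 20 + 40 patients it calculated, with no allowance for loss, so the stated 80% power is at best the power with complete IL-6 data

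*Protocol article*

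**What the plan says.** Section 2.4 (Sample size) of the protocol article names IL-6 as the main efficacy indicator and says "we chose the mean superiority test of 2 independent samples to estimate the sample size". The inputs are means that "were 6.14 and 6.21, and the combined standard deviation of the 2 groups was 0.14", a further figure described by "the optimal response rate was set to 0.04", and the instruction to "set *a* to 0.025 and *b* to 0.2". The software is said "to calculate the sample size for the experimental group as 20 and the control group as 40", and the section closes with "Finally, the total number of study samples is determined to be 60 cases".

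Section 2.1 (Design) has sixty participants "randomly assigned to the experimental or control group at a ratio of 1:2".

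Section 2.9 confirms that participants may drop out and adds "The test will also be withdrawn or terminated if the following criteria occur". Four grounds follow: reactions the patient cannot tolerate, serious adverse events, another complicating disease, and poor compliance.

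Section 3.2 measures IL-6 before treatment and weekly during it. Section 3.5 compares the groups by independent-sample t test.

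**The concern.** A sample size calculation returns the number of patients who must contribute data to the comparison. Section 2.4 goes from inputs to output to final total, with no step between the last two, so the number needed at analysis and the number randomised are the same. The same article expects some patients to leave. If leaving means that the IL-6 value is not available, the comparison has fewer than 20 + 40 patients and less power than section 2.4 implies.

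At stake is how a null IL-6 result is read. A reader who trusts b = 0.2 would give it more weight than the data could bear. The 1:2 allocation adds to this, because losing a given number of patients from the smaller foot bath arm costs more precision than losing the same number of controls.

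**Working it through.** **Inputs.** From section 2.4: means 6.14 and 6.21 (difference 0.07), SD 0.14, an additional figure of 0.04, a = 0.025, b = 0.2. From section 2.1: allocation 1:2. Two readings are assumptions: a is taken as one-sided, and 0.04 as some kind of margin.

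**Formulas.** With n1 experimental and n2 control patients, SE = SD × √(1/n1 + 1/n2) and the noncentrality is δ/SE. Power is the probability that a noncentral t with n1 + n2 − 2 degrees of freedom exceeds the 0.975 quantile of the central t.

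**Reproducing 20/40.** Three distances δ can be built from the printed figures. With all 60 patients, SE = 0.14 × √(1/20 + 1/40) = 0.0383.

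| Distance δ | Smallest 1:2 design with 80% power | Power at 20 + 40 |
|---|---|---|
| 0.07 (no margin) | 48 + 96 = 144 | 43.5% |
| 0.07 − 0.04 = 0.03 (superiority by a margin) | 258 + 516 = 774 | 11.7% |
| 0.07 + 0.04 = 0.11 (non-inferiority type) | 20 + 40 = 60 | 80.5% |

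Only δ = 0.11 gives the printed 20 and 40. There the noncentrality is 0.11/0.0383 = 2.87 on 58 degrees of freedom.

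**Effect of loss.** The documents give no loss rate, so a range is assumed. Loss here means patients with no usable IL-6 value.

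| Patients with IL-6 data | Loss | Power, δ = 0.11 | Power, δ = 0.07 |
|---|---|---|---|
| 20 + 40 | none | 80.5% | 43.5% |
| 20 + 39 | one control | 80.2% | 43.1% |
| 19 + 40 | one experimental | 79.2% | 42.2% |
| 19 + 38 | 5% | 78.4% | 41.6% |
| 18 + 36 | 10% | 76.2% | 39.7% |
| 17 + 34 | 15% | 73.7% | 37.8% |
| 16 + 32 | 20% | 71.0% | 35.9% |

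The rows for one lost patient show the asymmetry. At δ = 0.11 a lost control costs about 0.4 points and a lost experimental patient about 1.4.

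**Detectable difference.** The standardised difference detectable with 80% power is 0.780 SD at 20 + 40, 0.824 at 18 + 36 and 0.876 at 16 + 32. Multiplied by SD 0.14, these are IL-6 differences of 0.109, 0.115 and 0.123. All exceed the printed 0.07. These figures do not depend on how 0.04 is read.

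**The case against.** **The larger fault lies in the inputs.** This is correct. For the superiority test that section 2.4 names, 60 complete patients give about 43% power for a difference of 0.07, and about 12% if 0.04 is a superiority margin. A reader might infer from the missing allowance that 80% power is secure as long as nobody is lost. The printed inputs do not support that, and a loss allowance alone would not repair it. The allowance still has to be dealt with once the inputs are put right.

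**Withdrawal is not the same as a missing value.** This also stands. Section 2.9 governs leaving the trial. It does not say that withdrawn patients go unmeasured or are excluded, and with weekly sampling a patient who leaves midway may already have on-treatment IL-6 values. A reader might infer that section 2.9 guarantees a comparison with fewer than 20 + 40 patients. It makes that possible, not certain.

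**One lost patient need not take power below 80%.** At δ = 0.11, losing one control leaves 80.2%, so it would be too strict to say that 80% requires no loss at all. The slack is that one control; losing one experimental patient gives 79.2%.

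**The article is condensed.** A loss assumption could sit in a fuller document, and the discussion already concedes a small sample. That limits the weight of the point. It does not remove it, because the article prints both the calculated and the final number and they are equal. A loss assumption stated elsewhere would not change the fact that 60 contains no allowance for it.

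**Conclusion.** The point holds in a limited form. The addition 20 + 40 = 60 is correct. The weakness is that the number needed at analysis is also the number randomised, in a protocol that provides for withdrawal on four grounds. The stated b = 0.2 is therefore at best the power with complete IL-6 data.

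The size depends on assumptions. On the one reading that reproduces 20/40, a loss of 5% to 10% costs about 2 to 4 percentage points and a loss of 20% about 10. For the printed difference of 0.07, the start is about 43% and 20% loss brings it to about 36%. Both sets take a as one-sided, equal loss rates in the two arms, and loss meaning no IL-6 value. The point ranks below the reconciliation of the inputs in section 2.4.

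**What to change.** Keep 60 patients and amend section 2.4 in this order:

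1. Reconcile the inputs: what the 0.04 figure is, how it combines with the difference of 0.07, and whether the test is superiority as stated.
2. Say that 20 + 40 is the number needed at analysis.
3. State a range for the proportion of patients expected to have no IL-6 data, and restate the power, or the detectable IL-6 difference, for the numbers that remain, using the reconciled inputs.

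The figures of 76% at 10% loss and 71% at 20% should not be copied into the protocol unless the reconciled inputs really do give 80% at 20 + 40. If the difference of 0.07 stands without a margin, the matching figures are about 40% and 36%.

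Beyond the reconciliation, which is needed in any case, this costs a sentence or two and no extra patients. The downside is that the stated power becomes less favourable.
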